### Inclusion Criteria

Participants will be between 18–34 years, have experienced at least one unintended consequence from drinking in the previous 3 months as measured by the selected Screening Test: Young Adult Alcohol Problem Severity Test (YAAPST), have access to the Internet, and own a mobile phone on any plan. Non-drinkers will not be excluded from participation as they may experience unintended consequences due to their association with drinkers. Non-drinkers may socialize with drinking friends and be the “responsible” person in the group. As such, they may want to use the text message service to remind themselves of this responsibility. We did not want to exclude non-drinkers from the study as non-drinkers can be caught up in unintended negative consequences when out with drinking friends. The Alcohol Use Disorders Identification Test alcohol consumption questions (AUDIT-C) scores will identify these non-drinkers and we will control for them in the statistical analysis.

There will be no limit to the number of participants. Recruitment will remain open for 8–10 months.

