### Blinding and Randomization Allocation

Participants will be allocated 2:1 to the control and intervention groups, respectively, to ensure adequate numbers for study comparison. There is evidence of a high level of attrition in the control group in Internet-based interventions. Therefore, we chose the 2:1 allocation to reduce the risk of control group dropout. The researchers will be blinded to treatment allocation. Participants fulfilling the inclusion criteria will be asked to consent to the study and answer demographic, drinking, and consequences questions before gaining on-going access to the website. Participants will be randomized to each of the two groups by computerized central randomization using stratified blocks (block size = 6). Two stratification factors will be used: gender (male/female) and age (≤ 24 years and > 24 years) to ensure balance in these key prognostic factors between the intervention and control groups. Once randomized, intervention participants will receive an appropriate email with instructions and reminders for setting up and accessing their messages.

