### Treatment Effects

The relationship between frequency of text message use and behavior change (ie, change in reported drinking and/or change in safety behaviors) will be investigated. For each group, paired *t *tests will be used to assess the treatment effect between baseline and 3 months. Change from baseline to 3 months in drinking and consequences scores will be analyzed using linear regression and the model will include group and the baseline values. To assess the effect of factors such as age, gender, and ethnicity, adjusted linear regression analysis will be conducted. And if there are sufficient participants, subgroup analysis will be conducted.

Data collected at 6 months will be analyzed according to the preceding 3-month protocol. If there are sufficient data, repeated measures analysis will be run to compare the two groups across the full 6-month follow-up. Scatter plots will be generated to show the change in scores over time. Change in consequences score will be plotted at each follow-up assessment against message intensity (volume of messages sent) and correlation between these two variables will be calculated. Alcohol/consequences data will be plotted against frequency/intensity of messaging to give an indication of the messaging relationship on outcomes.

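### The stated between-group model leaves out the gender and age strata of the randomisation, and no model names the promised control for non-drinkers

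*Protocol article*

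**What the plan says.** All references are to the protocol article.

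- **Randomisation** (Blinding and Randomization Allocation). "Two stratification factors will be used: gender (male/female) and age", with age cut at 24 years, in blocks of six and at two controls to one intervention participant. The reason given is "to ensure balance in these key prognostic factors between the intervention and control groups".
- **Group comparison** (Treatment Effects). Change from baseline to 3 months in the drinking and consequences scores is analysed by linear regression, and "the model will include group and the baseline values". The 6-month data are to be handled in the same way, with a repeated measures analysis if the data allow.
- **Further regression** (same section, next sentence). "To assess the effect of factors such as age, gender, and ethnicity, adjusted linear regression analysis will be conducted". The article does not say how this model ranks against the one before it, or whether age enters as the stratum.
- **Non-drinkers** (Inclusion Criteria). They may enrol. AUDIT-C scores "will identify these non-drinkers and we will control for them in the statistical analysis".

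**The concern.** There are two separate mismatches.

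First, stratified randomisation makes the groups more alike on the strata than chance would. A regression that leaves the strata out still counts their variation as residual noise, so its standard error for the group effect does not reflect the balance the design has achieved. Precision already built into the design is thrown away. The adjusted regression would recover it, but it is presented as a study of the factors, not as the estimate of the treatment effect. The plan will therefore produce two group estimates without saying which one leads.

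Second, the eligibility section commits to an adjustment that the analysis section does not visibly carry out. This matters most for the consequences score, which the Abstract names as the primary outcome at 3 months. The natural baseline value in that model is the baseline consequences score, and that score does not tell drinkers from non-drinkers.

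The Objectives and Sample Size sections say the results will inform the sample size of a later trial. A residual variance taken from a model without the strata would carry any overstatement into that calculation.

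**Working it through.** **Inputs.** From the article: the covariates of the stated model, the two stratification factors (four strata), blocks of six and 2:1 allocation. The article gives no sample size, standard deviation, power or interval width, so there is no figure of its own to reproduce. The quantity that matters is the partial R² of the strata, meaning the share of outcome variance they explain after group and baseline score. It is not given, and 0 to 0.20 is an assumed range.

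**Formulas**, taking allocation as balanced within strata:

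- Standard error (and interval width) ratio, strata omitted to strata included: 1/√(1 − R²).
- Actual type I error of a nominal two-sided 5% test with strata omitted: 2 × [1 − Φ(1.96/√(1 − R²))].
- Ratio of residual variances, and so of sample sizes planned from them: 1/(1 − R²).

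| Assumed partial R² | SE ratio | Type I error, strata omitted | Variance ratio |
|---|---|---|---|
| 0 | 1.000 | 5.0% | 1.00 |
| 0.02 | 1.010 | 4.8% | 1.02 |
| 0.05 | 1.026 | 4.4% | 1.05 |
| 0.10 | 1.054 | 3.9% | 1.11 |
| 0.20 | 1.118 | 2.8% | 1.25 |

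Worked example for 0.10: 1/√0.90 = 1.054; 1.96 × 1.054 = 2.066; the two-sided tail beyond 2.066 is 0.039; 1/0.90 = 1.11.

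**Simulation check.** Four strata, blocks of six and 2:1 allocation, with assumed totals of 60, 150 and 300 and 4,000 replicates per setting.

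- Interval-width ratios matched the formula. At R² = 0.20 they were 1.117, 1.118 and 1.118. At R² = 0 they were 0.997, 1.000 and 1.000, so adjustment gains nothing when the strata do not predict the outcome.
- Rejection rates at R² = 0.20 were 2.6% to 3.4% without the strata and 4.6% to 5.2% with them. These rates are noisier: the Monte Carlo standard error is √(0.05 × 0.95/4000) ≈ 0.34 percentage points. Over all 15 settings the rates with strata ran from 4.0% to 5.4%.

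**Non-drinkers.** No arithmetic is possible, because their share and their difference in outcome are not given. Setting the sections side by side:

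- *Drinking score.* The baseline value in the model is lowest for non-drinkers, so it does part of the promised job. Non-drinkers are at the floor and cannot show a reduction.
- *Consequences score.* Every participant, drinker or not, must report at least one recent consequence to enter, so the floor argument does not apply here. The baseline consequences score does not identify non-drinkers, and the article does not say whether baseline drinking also enters this model.

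**The case against.** The case against has five parts.

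- **Age and gender are not ignored.** A reader might infer that the analysis omits them altogether. It does not, because the very next sentence plans a regression that includes them. This stands. What remains is that the model stated for the group comparison lacks the strata, while the one that has them is given another purpose.
- **No promise to adjust for the strata is broken.** A reader might infer one, but the article stratifies for balance and says nothing of adjusting the main model. The only undertaking concerns non-drinkers.
- **That undertaking is not shown to be abandoned.** The commitment names no model, the list of adjustment factors is open-ended, and baseline drinking serves part of the purpose. This is fair: the sections fail to connect but do not flatly contradict each other.
- **The error is on the safe side and may be negligible.** The group estimate stays unbiased, and every type I figure above is at or below 5%. With partial R² of 0.05 or less, the loss is under 3%. In a feasibility study with no powered test, that is modest.
- **The choice of main model could be left to the analysis plan.** This would answer a silent article. Here the covariates are stated, and a better set is available from data already held.

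**Conclusion.** The point holds in a limited form. The stated between-group model does not reflect the stratified randomisation. The cost is precision only: standard errors about 0% to 12% too large over an assumed partial R² of 0 to 0.20, probably towards the lower end, and nothing if the strata do not predict change beyond baseline. Inference is conservative. The documents support no claim of bias or of excess false positives, and the 11.8% figure is the top of an assumed range, not an expected loss.

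If the later trial's sample size were taken from this model's residual variance but that trial were analysed with the strata, it would be planned 0% to 25% too large over the same range.

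The non-drinker mismatch is real but narrow. The commitment is made, no model names it, and for the consequences score the baseline value would not fulfil it. Its numerical effect cannot be derived from the article.

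**What to change.** In Treatment Effects, state the main 3-month model as change on group, baseline value of the score, gender and age stratum (24 years or under, over 24). Use the same terms at 6 months and in the repeated measures analysis, and name this as the model that gives the leading group estimate.

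To carry out the undertaking in Inclusion Criteria, add baseline AUDIT-C, or a non-drinker indicator derived from it. Use the indicator only if non-drinkers are not too sparse; otherwise baseline AUDIT-C is the safer choice. Keep ethnicity for the secondary adjusted model.

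No new data are needed. Gender and age must be known before a participant can be randomised, and AUDIT-C is collected from everyone at baseline. The cost is a sentence or two of text and about three degrees of freedom: gender, age stratum and the AUDIT-C term.

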### Withdrawal Criteria

There are no withdrawal criteria for this study. Participants wishing to drop out of the study can do so by returning to the website to turn off their messages. The termination of messages will be the proxy measure of dropout rate.

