### Procedure to Account for Missing Data

Analysis will be on an intention-to-treat (ITT) basis. Those lost to follow-up will be included in the data analysis and are defined as those not using the messaging function or those who fail to complete the outcomes measures at 3 months and 6 months. Missing data will be replaced by the last observation carried forward (LOCF) with no change assumed since the last message sent. If feasible, sensitivity analyses will be performed excluding participants with missing outcome data to assess the robustness of the study findings.

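### The unadjusted correlation of change in consequences with self-chosen message volume can show a dose-response even if messages do nothing

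*Protocol article*

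**What the plan says.** Under Treatment Effects, the protocol article undertakes to examine how message use relates to behavior change and names the statistic: "Change in consequences score will be plotted at each follow-up assessment against message intensity (volume of messages sent) and correlation between these two variables"; that is, the "correlation between these two variables will be calculated". The purpose of the accompanying plots of drinking and consequences against messaging is "to give an indication of the messaging relationship on outcomes". In the same section, the between-group comparison of change from baseline is "analyzed using linear regression and the model will include group and the baseline values". No such adjustment is stated for the correlation.

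Three other parts of the article bear on it:

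- **Study Intervention.** Participants write and schedule their own messages. There is no cap on number or frequency, and messages run until the participant deactivates them.
- **Withdrawal Criteria.** "The termination of messages will be the proxy measure of dropout rate".
- **Procedure to Account for Missing Data.** Loss to follow-up covers "those not using the messaging function or those who fail to complete the outcomes measures at 3 months and 6 months". The imputation rule is: "Missing data will be replaced by the last observation carried forward (LOCF) with no change assumed since the last message sent". A sensitivity analysis without participants who lack outcome data is planned if feasible.

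**The concern.** Message volume is not randomized, and a change score carries the baseline score inside it. If people with worse baseline consequences schedule more messages, they will also tend to fall further by regression to the mean. Entry requires at least one recent consequence, so some average fall is plausible without any treatment effect.

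Separately, dropout and imputation are described in terms of messaging itself. If early stoppers send few messages and more often lack follow-up scores, LOCF records no change for many low-volume people while the rest move with the group average. That alone creates a gradient.

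The study is meant to inform the design of a later trial. A gradient of this kind could be taken as support for more intensive messaging, and one of the opposite sign could wrongly discourage it.

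**Working it through.** The protocol states no sample size, standard deviation, expected correlation or significance level for this analysis, so there is no figure to reproduce. The check asks what r would be if messages had no effect. Negative r means that more messages go with a larger fall.

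**Assumptions, none from the documents**

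- R, the correlation of baseline with follow-up score: 0.5 to 0.8 (0.6 or 0.7 where LOCF is involved).
- rho, the correlation of message volume with baseline score: -0.3, 0 or +0.3.
- Equal variances at baseline and follow-up; scores in SD units.
- For LOCF: the 40% with the lowest volume are imputed with zero change.
- Mean change: a fall of 0.15 to 0.5 SD, or a rise of 0.3 SD for the reverse case.

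**Route 1: baseline severity, no LOCF**

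If volume is related to follow-up only through baseline, the covariance of volume with change is rho × (R - 1), and the SD of change is sqrt(2(1 - R)). So r = -rho × sqrt((1 - R)/2).

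- rho = +0.3, R = 0.5: -0.3 × sqrt(0.25) = -0.15
- rho = +0.3, R = 0.6: -0.3 × sqrt(0.20) = -0.134
- rho = +0.3, R = 0.8: -0.3 × sqrt(0.10) = -0.095
- rho = 0: r = 0
- rho = -0.3: +0.09 to +0.15, a false signal of harm

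**Route 2: LOCF, rho = 0**

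Let mu be the mean change among those observed. With normally distributed volume, the covariance of volume with recorded change is mu × 0.386, where 0.386 is the normal density at the 40th percentile. The variance of recorded change is 0.6 × 2(1 - R) + 0.6 × 0.4 × mu².

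- mu = -0.3, R = 0.6: -0.116 / sqrt(0.480 + 0.022) = -0.16
- mu = -0.5, R = 0.6: -0.193 / sqrt(0.480 + 0.060) = -0.26
- mu = -0.3, R = 0.7: -0.116 / sqrt(0.360 + 0.022) = -0.19
- mu = 0: r = 0
- mu = +0.3: +0.16 (R = 0.6) or +0.19 (R = 0.7)

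A simulation in which the fall arises from selecting entrants on baseline score (mean fall 0.15 to 0.32 SD) gave -0.10 to -0.19.

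**Both routes, with selection on baseline (simulation)**

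- rho = +0.3: -0.16 to -0.24
- rho = -0.3: -0.06 to -0.14

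**How often this would look significant**

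The plan sets no test, so this is only for scale. By the Fisher z approximation, a spurious r of size 0.13 gives two-sided p < 0.05 in 25% of studies with n = 100 and 45% with n = 200. For r of size 0.20 the figures are 51% and 81%.

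**What removes it**

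- Baseline adjustment with LOCF values kept: still -0.09 to -0.19 under selection on baseline (rho from -0.3 to +0.3).
- Observed outcomes without baseline adjustment: route 2 goes and route 1 stays.
- Observed outcomes with baseline adjustment: 0.00 in every null setting tried.

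**The case against.** The strongest reply is that this is a secondary, indicative calculation in a feasibility study. Evidence of effect comes from the randomized comparison, which is adjusted for baseline and does not depend on who chose to send messages. No progression rule rests on the correlation. All of that stands and limits how much the point matters. It does not make the named statistic a sound one.

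Four stronger readings are tempting, and the documents do not support them.

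- **That a dose-response will appear.** Both routes need inputs that the protocol does not give. With volume unrelated to baseline and no mean change there is no bias, and the sign can reverse.
- **That low volume is tied to zero change by construction.** Messages repeat until deactivated, so someone who drifts away without switching them off keeps accumulating volume. LOCF is stated for missing data, and it is unclear whether a person who stops messaging but completes the questionnaire would be imputed, although the definition of loss to follow-up allows that reading. At 6 months the carried value may be the 3-month score, so change from baseline need not be zero.
- **That nothing in the plan guards against this.** The sensitivity analysis without missing outcomes, if done, removes the LOCF route. It leaves the baseline route.
- **That controls will be pooled into the correlation.** The article does not say which arm enters. That silence is not an error, but the revised sentence may as well settle it.

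**Conclusion.** The point holds as a statement of what can happen. With no message effect, the planned correlation can be of the order of -0.1 to -0.25 from baseline severity, LOCF or both. That rests on a volume-baseline correlation of about +0.3, a mean fall of 0.15 to 0.5 SD, and imputation concentrated in the lowest-volume 40%. Under other inputs it is zero or positive. The trial's randomized comparison is untouched. This is a cheap improvement to an indicative analysis and does not threaten the study's main conclusions.

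**What to change.** In Treatment Effects, replace the raw correlation with a linear regression of the follow-up consequences score on message volume and baseline consequences score. Fit it in the intervention arm, using observed outcomes and no LOCF values. Do the same for the drinking outcome. The scatter plots can stay, with imputed points left out.

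State that the result is an observational association and not a treatment effect. It may still be confounded, for example by motivation, which could drive both message use and improvement. Readiness to change is already collected at baseline and could be added as a covariate. The near-zero result above holds only when baseline score is the sole confounder and missingness depends only on message volume.

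The cost is about one sentence in the plan and a few lines of code, with no new data. The price is a smaller n for this analysis, since imputed values drop out, as do any controls who take up messaging after 3 months.

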### Procedure to Account for Missing Data

Analysis will be on an intention-to-treat (ITT) basis. Those lost to follow-up will be included in the data analysis and are defined as those not using the messaging function or those who fail to complete the outcomes measures at 3 months and 6 months. Missing data will be replaced by the last observation carried forward (LOCF) with no change assumed since the last message sent. If feasible, sensitivity analyses will be performed excluding participants with missing outcome data to assess the robustness of the study findings.

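### LOCF as the main missing-data method sets every 3-month non-responder's change to zero, which biases the group comparison when loss differs between arms and understates the SD passed to the RCT

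*Protocol article*

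**What the plan says.** The section Procedure to Account for Missing Data labels the analysis intention-to-treat and sets the rule: "Missing data will be replaced by the last observation carried forward (LOCF". The same sentence adds that nothing is taken to have changed after the participant's final message. The one alternative is conditional: "If feasible, sensitivity analyses will be performed excluding participants with missing outcome data to assess the robustness of the study findings".

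Four other parts of the article bear on this:

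- **Blinding and Randomization Allocation** states "There is evidence of a high level of attrition in the control group in Internet-based interventions" and gives that as the reason for the ratio: "Therefore, we chose the 2:1 allocation to reduce the risk of control group dropout". It reports no rate for either arm.
- **Inclusion Criteria** requires that participants "have experienced at least one unintended consequence from drinking in the previous 3 months as measured by the selected Screening Test". Consequences Measure uses the same instrument, with the same 3-month recall, as the outcome.
- **Treatment Effects** analyses change from baseline to 3 months by linear regression on group and baseline value, alongside paired t tests within each group. It mentions no allowance for imputed values.
- **Abstract and Objectives:** the abstract names change in unintended consequences at 3 months as the primary outcome. Objectives says the data will feed the sample size of the later RCT.

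**The concern.** Outcomes are collected at baseline, 3 months and 6 months. The last outcome before 3 months is therefore always baseline, and LOCF amounts to assigning zero change to everyone who does not answer. The wording ties the rule to the last message sent, but a message is not an outcome measurement, so this supplies no later value.

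If scores tend to fall in both arms for reasons unrelated to treatment, the arm with more non-responders gets more zeros and appears to improve less. The 2:1 ratio gives no protection, because the bias depends on the proportion missing in each arm and not on the number randomised.

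Two outputs are at stake: the 3-month estimate of effect, and the SD of change from which the RCT would be sized. Artificial zeros distort both.

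**Working it through.** **No stated figure to reproduce.** The article gives no sample size, SD, expected decline, dropout rate or significance level. What follows is algebra plus an illustration on assumed inputs.

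**Formula.** Let f be the mean fall without treatment, δ the extra fall due to the intervention, and mI and mC the proportions missing. Dropout is taken as unrelated to outcome within arm. After LOCF the mean change is -(1 - mI)(f + δ) in the intervention arm and -(1 - mC)f in control. The difference, intervention minus control, is

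-(1 - mI)δ - (mC - mI)f.

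- With δ = 0, what remains is -(mC - mI)f. It is zero if loss is equal, favours the intervention if control loss is higher, and favours control if intervention loss is higher.
- With δ > 0, the true effect is multiplied by (1 - mI). At 30% loss in both arms, 0.70 of it survives.
- Randomisation balances baseline between arms, so adjusting for baseline leaves the group term essentially unchanged.

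**Assumed inputs.** Gamma-Poisson counts with mean 3 and shape 1.5; entry at baseline ≥1; 150 or 300 participants, 2:1 control to intervention; no treatment effect; two-sided test at 1.96; 2,000 simulated trials per scenario.

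**Common fall under these inputs.**

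- P(0) = (1.5/4.5)^1.5 = 0.1925, so P(≥1) = 0.8075. Mean baseline after entry = 3/0.8075 = 3.715.
- P(1) = 1.5 × (2/3) × 0.1925 = 0.1925. Mean follow-up among entrants = (3 - 0.1925)/0.8075 = 3.477.
- Fall from selection alone = 3.715 - 3.477 = 0.238.
- With a further 20% decline in both arms, follow-up = 0.8 × 3.477 = 2.781, and the fall is 0.934.

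**Results.** Formula value of the null bias, with simulated type I error for the regression on LOCF data:

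| Missing, intervention / control | Fall | Bias by formula | Type I error |
|---|---|---|---|
| 20% / 40% and 20% / 50% | 0.238 | -0.048 and -0.071 | 6–8% |
| 20% / 40% | 0.934 | -0.187 | 10–16% |
| 20% / 50% | 0.934 | -0.280 | 15–27% |
| 30% / 40% | 0.934 | -0.093 | about 7–8% |
| 30% / 30% | either | 0 | about 5% |
| 40% / 20%, N = 300 | 0.934 | +0.187 | 12% |

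Simulated biases agree with the formula. One separate run at 20%/50% without decline gave 8.7%. The Monte Carlo standard error near 8% is √(0.08 × 0.92/2000) = 0.6 points, so the runs are consistent. The same regression on observed outcomes had bias near 0 and type I error of 4–6% throughout.

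**Precision.** At N = 300, 20%/40% missing and the decline, the LOCF model standard error is 0.227, against 0.298 on observed data: 1 - 0.227/0.298 = 24% smaller. Against the LOCF estimator's own sampling spread (0.239) it is 1 - 0.227/0.239 = 5% too small.

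**SD for the RCT.** In the same loss and decline scenario the SD of change is about 2.06 under LOCF and 2.46 on observed data. (2.06/2.46)² = 0.70, so the variance is about 30% too low. Required sample size is proportional to variance, so an RCT sized on it for a fixed target difference would be about 30% too small.

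**The case against.** The strongest reply has five parts.

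**Selection is not the main driver.** A reader might infer that a baseline inflated by the entry criterion creates a large spurious benefit. The criterion is only one consequence or more, and under the assumed model it produces a fall of 0.24 and a small bias. The larger figures need a general decline in both arms, which the documents do not state. This stands.

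**Direction is not established.** A reader might infer that the plan expects higher loss in control than in the intervention arm. It says control attrition is high in Internet-based interventions generally; the comparison between arms is an inference from the reason given for the 2:1 ratio. The missing-data section also counts people not using the messaging function as lost, although controls have no such function for 3 months. Loss is therefore not defined comparably across arms, and the direction could change. This stands.

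**Bias under data missing completely at random.** It is tempting to say that LOCF biases the null comparison even then. It does so only when loss differs by arm. With equal loss the null comparison is unbiased, and only a true effect is attenuated.

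**Interval too narrow.** The model standard error is only about 2–11% below the LOCF estimator's own spread when control loss is higher. The main fault is false precision relative to the data actually observed.

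**A complete-case analysis is planned, and this is a feasibility study.** That analysis would reveal the problem in these scenarios, but the article makes it conditional. The study has no stated power or significance-based decision, which lowers the severity. It does not remove the point, since the effect and the SD are meant to inform the RCT.

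**Conclusion.** The point holds in limited form. LOCF is a stated choice, and at 3 months it means zero change for every non-responder. Unequal loss combined with any common fall then biases the comparison, and a true effect is attenuated. The likely direction favours the intervention, given the article's own remark on control attrition, but it is not certain.

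The size cannot be fixed from the documents. Under the assumed counts it runs from negligible (equal loss, or a small gap with selection alone) to about -0.28 points with type I error up to 27% (20%/50% missing, 20% decline, 300 participants). The loss of about 30% of the variance of change rests on the same assumptions, at 20%/40% missing with the decline.

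The good performance of the observed-data regression rests on dropout being unrelated to outcome given baseline and group. Severity is moderate: the estimate serves planning and is not confirmatory. The documents do not support treating this as a fatal flaw, nor requiring a formal departure-from-missing-at-random analysis at this stage.

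**What to change.** 1. Make the main 3-month analysis the baseline-adjusted regression already planned, fitted to observed outcomes. A likelihood-based repeated-measures model, or multiple imputation by arm from baseline variables, would also serve. With a single post-baseline time point these add little to the regression.
2. Report this analysis unconditionally by deleting the words that make it depend on feasibility, and demote LOCF to a sensitivity analysis.
3. Estimate the SD of change for the RCT from observed data only.
4. Report the proportion missing the 3-month outcome by arm, defined by questionnaire completion alone, so that loss means the same in both arms.
5. At 6 months, do not carry controls' 3-month values forward as if follow-up were unchanged: the Control group section says controls are invited to use the intervention after 3 months.

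The cost is a little programming and a somewhat wider confidence interval. No extra data collection is needed.
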